## Abstract

**Background:**

Spinal cord injury (SCI) leads to a profound muscular atrophy, bone loss and bone fragility. While there is evidence that exercising paralysed muscles may lead to reversal of muscle atrophy in the chronic period after SCI, there is little evidence that exercise can prevent muscle changes early after injury. Moreover, whether exercise can prevent bone loss and microarchitectural decay is not clear.

**Methods/Design:**

A multi-centre, parallel group, assessor-blinded randomised controlled trial will be conducted. Fifty participants with acute spinal cord injury will be recruited from four SCI units in Australia and New Zealand. Participants will be stratified by site and AIS status and randomised to an experimental or control group. Experimental participants will receive a 12-week programme of functional electrical stimulation (FES)-assisted cycling. Control participants will receive a 12-week programme of passive cycling. The primary outcome is muscle cross-sectional area of the thigh and calf measured using magnetic resonance images (MRI) of the leg. Secondary outcomes include serum biomarkers of SCI osteoporosis (sclerostin, P1NP and β-CTX), markers of immune function (IL-6, IL-10, FGF2, INF-γ, TNF-α), neurological function, body composition, depression and quality of life. Leg MRIs will be measured by a single blinded assessor based in Melbourne. Serum samples will be analysed in a central laboratory. All other characteristics will be measured at baseline and 12 weeks by blinded and trained assessors at each site. The first participant was randomised on 27 November 2012.

**Discussion:**

The results of this trial will determine the relative effectiveness of a 12-week programme of FES-assisted cycling versus passive cycling in preventing muscle atrophy and maintaining skeletal integrity after spinal cord injury.

**Trial registration:**

ACTRN12611001079932 (18 October 2011)

## Background

Spinal cord injury (SCI) leads to a profound muscular atrophy, bone loss and bone fragility [1–3]. Fractures lead to a marked deterioration in bone quality, and compromise rehabilitation and quality of life [4].

Furthermore, recent advances have identified mechanisms that link muscle and bone metabolism, thereby identifying such tissues as endocrine organs [5, 6]. The discovery that muscle-secreted factors contribute to osteocyte viability [7] suggests a link between disuse and endocrine functions of bone and between muscle endocrine action and susceptibility for chronic disease [8, 9]. Such developments have highlighted inter-relationships between the aetiologies of sarcopenia and osteopenia [10], cardinal features of secondary disuse disorder such as occurs after SCI [11, 12]. Recognition that SCI involves an ‘endocrine syndrome’ [13, 14] has advanced our understanding of regulatory mechanisms that contribute to the clinical features of this catastrophic injury. Given that muscle-secreted factors (myokines) have endocrine and other actions, the role of skeletal muscle contraction induced by exercise following SCI warrants closer attention.

Thigh girth reduces by 50% within 3 weeks of SCI [15]; thickness of muscle bulk, measured using ultrasound, reduces by 40% in the first month [16]. A magnetic resonance imaging (MRI) study of changes in muscle cross-sectional area (CSA) over the first few months after SCI showed that the mean CSA of the quadriceps, hamstring and adductor muscle groups declined by 16%, 14% and 16% respectively [17].

Muscle is a dynamic tissue capable of adapting its morphology depending on the functional demands placed on it. There is evidence that exercising paralysed muscles through functional electrical stimulation (FES)-assisted cycling leads to reversal of atrophy [18]. Furthermore, in rats with spinal transection, passive exercise in the form of pedaling on a motor-driven cycle results in activation of muscle satellite cells and reversal of hindlimb muscle atrophy. This effect is more marked in muscles with slow oxidative fibres such as soleus [19].

It is still unknown whether unloading of the bones in the paralysed extremities is the only factor causing rapid bone loss below the level of injury, or if other factors such as neuronal, humoral and vascular adaptations after a SCI are also involved [20, 21]. Muscle forces create the peak forces acting on bone, a relationship summarised by the mechanostat theory [22], which predicts that bone mass, strength and size will respond to increasing muscle maximal forces during bone growth, or the loading of mature bone. Unloading through disuse or immobilisation will have a negative effect on bone mass and strength, both through muscle atrophy and local regulators of cell phenotype, within the bone tissue microenvironment.

Sclerostin, encoded by the *sost* gene, is a Wingless-Int (Wnt) signalling pathway antagonist secreted by osteocytes and is a potent inhibitor of bone formation [23]. Compared to other bone-related proteins, sclerostin is considered a candidate biomarker for SCI-induced osteoporosis [24]. Sclerostin is increased by unloading and suppressed by loading, a feature observed at least in the first few years after SCI [25, 26]. In addition to the mechanical loading of bone through muscle contraction, muscle myokines released from contracting muscles may protect osteocytes from undergoing cell death [27].

One study has used FES early after injury to *prevent* muscle changes rather than *reverse* them when losses are well advanced. Baldi *et al*. [12] compared FES-assisted cycling with FES-induced isometric muscle contractions commencing within the first 12 to 15 weeks of injury. Control subjects who had had no exercise lost 21 to 27% of muscle mass. FES-cycling, but not FES-induced isometric exercise, prevented loss of lower limb lean body mass and gluteal lean body mass at both 3 and 6 months.

Whether exercise can *prevent* bone loss and microarchitectural decay or reverse it when established is not clear. A regimen of FES-assisted isotonic contractions instituted early after SCI did not lead to an osteogenic effect in the lower limbs, measured using dual energy X-ray absorptiometry [28]. A 2010 systematic review [29] has concluded that FES-cycling does not improve or maintain bone at the tibial diaphysis in the acute phase, but may increase/maintain lower extremity bone mineral density (BMD) in the chronic phase after SCI [30], the implication being that site-specific bone adaptation is both time- and dose-dependent and thus, mechanisms of bone adaptation may differ in acute and in established SCI.

In this trial, we will provide an exercise programme that involves FES-cycling against increasing loads as early as practicable after SCI, commencing when the individual is still confined to bed. We hypothesise that muscle activation will prevent muscle atrophy. In addition, we hypothesise that mechanical strains associated with loading and changing leg position during cycling will inhibit sclerostin levels and thereby preserve skeletal structure by reducing inhibition of bone formation and reduce increased bone resorption at the cellular level seen early after injury.

## Methods

The trial was registered on the Australian and New Zealand Clinical Trials Registry (ACTRN12611001079932) on 18 October 2011. The first participant was randomised on 27 November 2012, and the final participant on 31 March 2014.

### Design

A multi-centre, assessor-blinded, randomised controlled trial will be conducted. Experimental group participants will undertake an intensive 12-week programme of FES-assisted cycling, while control group participants will undertake a passive cycling programme over the same period. The trial will be conducted in four spinal units in Australia and New Zealand. Ethical approval has been obtained from the Human Research Ethics Committees at Austin Health in Melbourne (H2012/04476), Royal Perth Hospital in Perth (EC 2012/080), Princess Alexandra Hospital in Brisbane (HREC/12/QPAH/085) and the Multi-region Ethics Committee in New Zealand (MEC/12/02/020) and at the University of Melbourne (Trial Sponsor, HREC 1237599). Participants will be provided with information sheets and written informed consent will be obtained prior to recruitment and baseline assessment. See Table 1 for the schedule of enrolment, interventions, and assessments.

**Table 1 Tab1:** **Standard Protocol Items: Recommendations for Interventional Trials (SPIRIT) checklist: schedule of enrolment, interventions, and assessments**

	Enrolment	Allocation	Intervention	Post-intervention
TIMEPOINT	***-t*** _***1***_	0	12 weeks	12 weeks
**ENROLMENT:**				
**Eligibility screen**	X			
**Informed consent**	X			
**Medical clearance**	X			
**Allocation**		X		
**INTERVENTIONS:**				
***FES-assisted cycling***				
***Passive cycling***				
**ASSESSMENTS*:**				
***Muscle cross-sectional area of thigh and calf (1° outcome measure)***	X			X
***Serum sclerostin***	X			X
***Other serum biomarkers***	X			X
***Muscle mass***	X			X
***ISNCSCI Motor and Sensory Scores***	X			X
***Depression (HADS)***	X			X
***Quality of Life***	X			X
***(HUI3, AQoL, WHOQoL-Bref)***				

*1-week window allowed for assessments.

FES = functional electrical stimulation; ISNCSCI = International Standard for Neurological Classification of Spinal Cord Injury; HADS = Hospital Anxiety and Depression Scale; HUI3 = Health Utilities Index Mark 3; AQoL = Assessment of Quality of Life; WHOQoL-Bref = WHO Quality of Life-Bref.

### Participants

Fifty participants with new acute SCI admitted to one of the four trial sites will be recruited.

### Inclusion criteria

Participants will be included if they:Have sustained a complete or incomplete SCI above T12 no more than 3 weeks previouslyHave undergone internal fixation of their spinal fracture or whose fracture is considered sufficiently stableAre medically stableAre able to provide informed consentHave medical and surgical clearance to participate in the study

### Exclusion criteria

Under 18 years of ageAmerican Spinal Injury Association Impairment Scale (AIS) D (50% of the muscles below the injury level are scored as 3 or above) at baselineIn halo or other tractionIn the ICUPressure ulcersPeripheral nerve lesionLong bone or pelvic fractureLower limb amputationMetabolic bone disease, including lytic or renal bone disease, or senile osteoporosisExposure to drugs that affect bone metabolism (amino-bisphosphonate, high-dose glucocorticoids, cyclosporine, anti-epileptic drugs (AEDs))Known contraindications to FES (cardiac pacemaker, epilepsy, pregnancy)Any other contraindications to participating in exercise programmes, or outcome assessments, as advised by the treating physicianEnglish language competency insufficient to understand research procedures and provide informed consent.

### Randomisation

Participants will be randomly assigned to either the experimental or control group with a 1:1 allocation as per a computer-generated randomisation schedule stratified by participating site and injury status (AIS) A/B or AIS C). The randomisation schedule will be under the control of a central randomisation unit, independent of the trial, located at Neuroscience Trials Australia in Melbourne. A participant will be considered to have entered the trial once his/her randomisation is revealed to the site coordinator.

### Intervention

All participants will attend the assigned exercise programme for 48 sessions over 12 weeks, with an intended frequency of 4 times weekly.

#### Experimental group

Participants in the experimental group will receive FES-assisted cycling using a Hasomed RehaStim FES Unit attached to a MOTOmed cycle (Hasomed GmbH, Magdeburg, Germany) while they are confined to bed, and an RT300 cycle (Restorative Therapies, Baltimore, MD, USA) when they are able to sit in a chair. Surface electrodes will be applied over the belly of the quadriceps, gluteal, and hamstrings muscles according to a standardised protocol [31]. The pedal cadence will be set to 15 to 50 rev.min^−1^ Stimulation intensity will be gradually increased to a maximum of 140 mA with a pulse width of 0.3 ms at a frequency of 35 Hz [31, 32]. Participants will exercise at the maximal power output possible at their level of recovery. Therapists will evaluate the degree of muscle contraction, power output and fatigue, and adjust settings appropriately to maximise time, intensity, and power of training with a principle of overloading the muscle. When fatigue occurs, cycling can be stopped and then re-commenced after a 5-minute break if muscle contraction can be re-elicited. For participants with some degree of volitional muscle activity, the settings will be adjusted to ensure that resistance is maintained.

Participants will undertake 30 minutes of cycling on 4 days/week for 12 weeks, initially in intermittent periods of exercise with rest breaks, but progressing to a maximum of 60 minutes as deemed appropriate by the supervising therapist/assistant. This can be undertaken as a single session or split into two sessions, depending on the participant’s performance and the availability of staff. All aspects of each training session will be recorded.

#### Comparator group

Participants allocated to this group will undertake up to 60 minutes passive cycling on 4 days/week for 12 weeks at identical pedal cadence to the Experimental Group. Similar to the Experimental Group, cycling while the participant is confined to bed will be with the MOTOmed Letto device (Hasomed GmbH, Magdeburg, Germany) and, once mobilised into a wheelchair, may use the RT300 cycle (Restorative Therapies, Baltimore, MD, USA) but without FES-evoked contractions.

#### Follow-up period

All participants will complete a post-intervention visit at the end of the 12-week intervention period. Assessments completed at baseline will be repeated. A follow-up phone call will be made 1 month after this visit to check on progress or adverse events in the intervening period.

#### Quality assurance

To ensure that treatments are of a high standard and delivered in accordance with the trial protocol, therapists responsible for administration of the exercise programmes will attend workshops where they will be trained in the delivery of the treatment programme and in assessment procedures. Therapists will also be provided with a written protocol and standardised case report forms for documentation of assessments and interventions.

### Assessments

Assessments will occur at baseline, and at 12 weeks after the commencement of the intervention. All assessments will be undertaken by therapists blinded to group allocation. Any inadvertent unblinding of assessors will be reported.

### Primary outcome

#### The primary outcome measure is muscle cross-sectional area of the thigh and calf at 12 weeks

Magnetic resonance images of the leg and thigh will be collected with a 1.5-Tesla magnet. Fifteen transaxial images, 1 cm thick and spaced 0.5 cm apart will be taken from the knee joint to the ankle joint (leg) and from the hip joint to the knee joint (thigh) using a whole-body coil. Markings on the mid-leg and mid-thigh aligned with cross-hairs on the imager will allow for similar positioning during repeat scans. The participants’ feet will be strapped to a brace to maintain the ankle joint at approximately 90° and the knee and hip joints extended. Participants will wear anti-embolism stockings for 30 minutes prior to imaging to minimise fluid shifts in the leg.

### Secondary outcome measures

To control for sources of pre-analytical variability, participants will be required to fast for 8 hours before blood is drawn between 0800 and 0900 hours (35 ml per sample). Serum samples will be collected at baseline, 1, 2, 3, 4, 8 and 12 weeks (end of intervention). All samples will be separated and stored at ─20°C until assayed in a central laboratory, and will be destroyed using standard laboratory techniques after the completion of the study.

### Serum sclerostin

Serum sclerostin will be measured using ELISA incorporating a biotinylated antibody/horseradish peroxidase-streptavidin for detection of the analyte. The detection limit of the sclerostin ELISA is 0.18 *mg.mL*^*−1*^ and the intra-assay coefficient of variability (CV) is between 6 to 10% [33].

### Other serum markers

The bone biomarkers N-propeptide of type I procollagen (P1NP) and β-isomerised C-terminal telopeptide of collagen type I (β-CTX) will be measured using the electrochemiluminescence sandwich immunoassays (both Elecsys 1010 Analytics, Roche Diagnostics, Mannheim, Germany).

The total P1NP assay detects the monomer and trimeric forms of the molecule represented in the serum. The reference standards given by the manufacturer for this assay (imprecision 1.8 to 2.9%) independently were validated (1.4 to 2.3%) ([34]. The inter-assay CVs are 1.4%, 1.7% and 2.0% at 74 μ*g.L*^*−1*^, 508 μ*g.L*^*−1*^ and 978 μ*g.L*^*−1*^, and intra-assay CVs are 2.0% and 2.3% at 47 μ*g.L*^*−1*^ and 643 μ*g.L*^*−1*^[34].

The monoclonal antibodies used in the Elecysis B-Cross Laps assay recognise all fragments of the β-δAA octapeptide of type 1 collagen. Intra-assay precision (CVs) given by the manufacturer is 4.6%, 1.8% and 1.0% at 0.08 *ng.mL*^*−1*^, 0.39 *ng.mL*^*−1*^ and 3.58 *ng.mL*^*−1*^. Total precision (CV) is 4.7%. 4.3% and 1.6% at 0.08 *ng.mL*^*−1*^, 0.39 *ng.mL*^*−1*^ and 3.58 *ng.mL*^*−1*^ respectively.

Biomarkers of immune function (systemic low-level inflammation), which also are myokines, will be assessed using a MILLIPLEX MAP Human Cytokine/Chemokine Magnetic Bead Panel Immunology Multiplex Assay read with a Luminex xMAP® platform (Merck Millipore, Darmstadt, Germany) in a magnetic bead format for the determination (*pg.ml*^*−1*^) of: IL-1β, IL-6, IL-10, IL-15, INF-γ, fibroblast growth factor 2 (FGF2), CX3CL1 (fractalkine), CCL2 (monocyte chemotactic protein-1: MCP-1), TNF-α, vascular endothelial derived growth factor (VEGF) and brain-derived neurotrophic factor (BDNF). Precision data given by the manufacturer estimate accuracy as 87 to 107%. Intra-assay and inter-assay CVs are given as 2 to 13% and 5 to 19%, respectively.

### Muscle mass

Muscle mass will be determined using standard anthropometric methods (measurement of lower limb girths and skinfold thickness) [35] according to the International Society for the Advancement of Kinanthropometry (ISAK) standards. The intraobserver reliability of anthropomentry is high (R > 0.9) [36].

### ISNCSCI motor and sensory scores

Motor and sensory recovery will be measured using the International Standard for Neurological Classification of Spinal Cord Injury (ISNCSCI) [37]. The motor score is derived from testing strength of five key upper limb and five key lower limb muscles bilaterally with the subject positioned in the supine position (for example, elbow flexors, wrist extensors, hip flexors, quadriceps, dorsiflexors) on a scale of 0 = no contraction to 5 = normal resistance through full range of motion. Scores are summed to give a total possible score of 50 for the upper extremities and 50 for the lower extremities. The sensory test involves testing pin-prick and light-touch sensation at key points representing each dermatome. Pin-prick and light-touch sensation of each dermatome are separately scored on a 3-point scale (0, 1 and 2). Scores will be summed to give a total possible score of 224, where a higher score indicates better sensation than a lower score. The total ISNCSCI motor, light-touch and pin-prick scores are highly reliable when assessed by experienced examiners [38].

This assessment will be used during the baseline visit to confirm the participant’s motor, sensory and neurological levels as well as the AIS classification, which indicates the degree of completeness of the spinal cord lesion prior to randomisation and then again at the post-intervention assessment.

### Depression

Depression will be measured using the Hospital Anxiety and Depression Scale (HADS) [39], which has been found to be valid [40] and reliable [41] for people with SCI.

### Assessment of Quality of Life (AQoL-8)

The AQoL-8 is a multi-attribute utility instrument. It will be used to evaluate whether the study intervention improves participants’ quality of life as well as for an economic evaluation of the intervention’s cost-effectiveness. The AQoL-8 is a self-administered 8-item questionnaire [42] with excellent test-retest reliability [43].

### Health Utilities Index Mark 3 (HUI-3)

HUI-3 is a measure of health-related quality of life widely used in population health surveys, clinical studies and cost-utility analyses. HUI-3 includes eight attributes (vision, hearing, speech, ambulation, dexterity, emotion, cognition and pain), with five or six levels for each attribute. HUI-3 is reliable [44] and is able to discriminate various aspects of burden associated with chronic conditions as well as describing the differences in overall health-related quality of life levels [45].

### WHOQoL-Bref

The WHOQoL-Bref questionnaire was designed by an international collaboration on quality of life by the World Health Organisation. It contains 26 questions about many different aspects of quality of life, with some additional questions about the person and his/her health. It has good test-retest reliability [46] and has been found to be a valid measure in people with SCI [47].

### Statistical analyses

#### Sample size

The power analysis is for a one-way fixed effects analysis of covariance (ANCOVA) with two levels that correspond to FES cycling and passive cycling arms of the study. This analysis includes baseline value of muscle CSA in the thigh and calf as a covariate, and uses the value of muscle CSA in the thigh and calf at week 12 as the primary outcome. Based on available pilot data [17], the participants in the passive cycling arm are likely to lose around 33% of the baseline muscle CSA (mean = 75, SD = 20) over a period of 12 weeks after SCI (measured using MRI). Assuming this loss could be contained to 10% by the proposed FES cycling intervention, thus resulting in mean changes of 25 (SD = 20) and 7.5 (SD = 20) for passive cycling and FES cycling respectively, the total sample size of 42 patients equally distributed between FES cycling and passive cycling arms will yield power of 0.8 to reject the null hypothesis at 0.05 level of significance. The ANCOVA is conservative (that is assuming no correlation between the baseline and follow-up measures) and non-directional (that is two-tailed) which means that an effect in either direction will be interpreted. Allowing for a15% drop-out rate, the final sample size for this study is calculated to be 50 patients equally distributed between FES cycling and passive cycling arms.

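### The sample size takes a 33% passive-arm loss of muscle CSA from reference [17], but the Background reports 14% to 16% from that same reference, and the article does not reconcile them

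*Protocol article*

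**What the plan says.** The Sample size section opens its justification with "Based on available pilot data [17" and states that "the participants in the passive cycling arm are likely to lose around 33% of the baseline muscle CSA", "over a period of 12 weeks after SCI (measured using MRI". Baseline CSA is given a mean of 75 and an SD of 20. The section assumes that FES cycling would hold the loss to 10%, so the mean changes are 25 and 7.5 units, each with SD 20. It concludes that "the total sample size of 42 patients equally distributed between FES cycling and passive cycling arms will yield power of 0.8" at the two-sided 0.05 level, with no baseline/follow-up correlation assumed. A 15% drop-out allowance raises the total to 50.

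The Background describes reference [17] as an MRI study of "changes in muscle cross-sectional area (CSA) over the first few months after SCI" and reports that "the mean CSA of the quadriceps, hamstring and adductor muscle groups declined by 16%, 14% and 16% respectively [17".

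The Background also gives three other figures for early loss, each from a different reference. These are a 50% fall in thigh girth within 3 weeks, a 40% fall in ultrasound muscle thickness in the first month, and this result from an early-exercise study: "Control subjects who had had no exercise lost 21 to 27% of muscle mass".

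**The concern.** The same reference, imaging method and type of measurement appear twice, and the planning figure is about twice the reported one. The passive-arm loss drives the calculation, because it sets the gap that FES cycling can close. The design difference of 17.5 units is 23% of baseline, which is more than the whole thigh loss that the Background quotes from [17].

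If the passive arm loses about as much as the Background reports, an intervention that only prevents loss cannot produce the planned difference. A non-significant result could then be read as evidence against FES cycling from a trial described as having 80% power, when the trial had much less chance of showing a benefit.

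**Working it through.** **Inputs from the Sample size section.** Baseline mean 75, SD 20, passive-arm change 25, FES change 7.5, 21 per arm, two-sided alpha 0.05, correlation r = 0, drop-out 15%.

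**Input from the Background.** Loss of 14% to 16% in the thigh groups, attributed to [17].

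**Step 1: reproduce the stated figure.**
- Difference = 25 − 7.5 = 17.5, and 17.5/75 = 23% of baseline.
- Normal approximation: n per arm = 2 × (1.960 + 0.842)² × 20² / 17.5² = 20.5, so 21 per arm and 42 in total. Power at 21 per arm is 0.81.
- Noncentral t with 39 degrees of freedom (42 less two arms and one covariate): standard error = 20 × √(2/21) = 6.17, noncentrality = 17.5/6.17 = 2.84, power = 0.79.
- Drop-out: 42/0.85 = 49.4, so 50.

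The stated figures follow from the stated inputs.

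**Step 2: replace 33% by 14% to 16%.** SD 20 is kept, which is an assumption. Two FES effects are taken:
- Complete prevention: 0.14 × 75 = 10.5 and 0.16 × 75 = 12.0 units.
- The plan's own proportional saving, 17.5/25 = 70% of the loss: 0.7 × 10.5 = 7.35 and 0.7 × 12.0 = 8.4 units.

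**Step 3: allow for correlation.** The documents give no value of r, so r = 0.7 is an assumption. If 20 is the SD of the week-12 value, the ANCOVA residual SD is 20 × √(1 − 0.7²) = 14.28 and the standard error is 14.28 × √(2/21) = 4.41.

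Power with 21 per arm (noncentral t, 39 degrees of freedom):

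| FES effect | Difference (14% to 16% loss) | r = 0 | r = 0.7 |
|---|---|---|---|
| All loss prevented | 10.5 to 12.0 | 0.38 to 0.47 | 0.64 to 0.76 |
| 70% of loss prevented | 7.35 to 8.4 | 0.21 to 0.26 | 0.37 to 0.46 |

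The upper entry in the first row at r = 0 is 0.475 to three places (0.4747). If all 50 patients were measured (25 per arm), that row at r = 0 would be 0.44 to 0.55. For 0.80 with 21 per arm, complete prevention of a 16% loss needs r of about 0.74.

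**Step 4: smallest difference detectable at 80% with 42 completers.** It is 17.7 units (24% of baseline) at r = 0, and 17.7 × 14.28/20 = 12.7 units (17% of baseline) at r = 0.7. Both exceed 12.0 units, which is the whole of a 16% loss.

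**Step 5: could the calf explain the gap?** The three thigh figures average (16 + 14 + 16)/3 = 15.3%. For thigh and calf together to average 33% at equal weights (an assumption), the calf would have to lose 2 × 33 − 15.3 = 50.7%, or about 51%.

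**The case against.** The strongest reply is that the two figures may describe different things. The Background lists thigh muscles only, over a loosely stated period, while the outcome covers thigh and calf at 12 weeks. Reference [17] may report a calf loss, another interval or another comparison that supports 33%. This stands as a limit: the documents cannot show that the 33% is false. It does not remove the contradiction, since the article gives both figures, credits both to one source and does not explain the gap.

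Second, other evidence in the Background lies above 33%: the 50% fall in girth and the 40% fall in ultrasound thickness. This also stands. A reader might infer that every other figure in the article is below 33%, citing the 21% to 27% loss of muscle mass. That is wrong. The 21% to 27% is itself not a CSA figure, and that study began exercise within 12 to 15 weeks of injury, whereas this trial enrols within 3 weeks. The girth and thickness figures do not rescue the 33% either, because they are other measures from other references, and some of that early loss could precede this trial's baseline.

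Third, r = 0 is a worst case, and the article says that its ANCOVA assumption is conservative. That is fair, so results at r = 0.7 are shown. The conservatism concerns correlation only and does not bear on the assumed loss.

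A reader might also hold the FES loss at 10% against a passive loss of 14% to 16%, which gives power near 0.1. That is a harsher scenario than the plan's, because it cuts the assumed benefit from 70% of the loss to between 4/14 = 29% and 6/16 = 38%. It is not relied on here. Nor are the entry delay of up to 3 weeks and the active nature of the comparator. Both could lower the passive-arm loss, but the article quantifies neither, and its evidence of reversal with passive cycling comes from rats.

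**Conclusion.** The point holds as an unreconciled contradiction in the input that drives the sample size. A reader might infer an arithmetic error, but there is none: 42, 0.8 and 50 all follow from the stated inputs. A reader might also infer that the trial's true power is below one half. The documents do not establish that, because reference [17] is not at hand and the outcome includes the calf.

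What they do support is conditional. If the passive-arm loss is what the Background reports, and the SD is 20, power with 42 completers falls short of 0.8 in each case in the table, even with complete prevention and a correlation of 0.7. The range is wide, from 0.21 to 0.76, because neither the correlation nor the SD under a smaller loss is known. As the article stands, its power of 0.8 rests on a loss that its own account of the source does not bear out.

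**What to change.** Reconcile the two uses of reference [17] by stating in the Sample size section which muscle group, interval and comparison the 33% comes from.

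If the 33% cannot be supported, replace the single power of 0.8 with power for passive-arm losses from 14%–16% up to 33%. State the FES effect and the correlation assumed for each. Add the smallest difference detectable at 80% with 42 completers: 17.7 units at r = 0 and 12.7 units at r = 0.7.

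The change is confined to one paragraph. The Trial status section says that recruitment has ended. No patients are added, and the outcome, test and analysis are unchanged. If the 33% has a clear basis, the cost is one sentence. If not, the cost is a less favourable stated power.
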